3.2 Twenty-four hour Holter monitoring

Twenty-four hour Holter monitoring will be performed with time domain and frequency domain before HUTT at baseline and after 30 days treatment in all VVS patients.

Time domain parameters

1. standard deviation of NN intervals (SDNN)
2. standard deviation of all 5-min average NN intervals (SDANN)
3. square root of mean of the sum of squares of successive NN interval differences (rMSSD)
4. number of successive NN interval differing by >50ms divided by the total number of successive NN intervals (pNN50)

Frequency domain parameters

1. low frequency (LF): at frequency between 0.04--0.15 Hz
2. high frequency (HF): at frequency between 0.15--0.40 Hz
3. and the low frequency/high frequency ratio (LF/HF)

3.3Detailed procedures of the modified Valsalva manoeuver (MV)

3.3.1 Expiration strength grades and breath-hold time of the modified MV.

Expiration strength is divided into 3 grades (Grade A = 20 mm Hg, Grade B = 30 mm Hg and Grade C = 40 mm Hg). Expiration strength is controlled by blowing into a tube connected to sphygmomanometer. Breath-hold time is divided into 2 lengths (1 = 8 seconds, 2 = 15 seconds).

3.3.2 Three steps of the modified MV

3.3.2.1 Threshold of MV

MVM group patients will be asked to perform MV in the order of A1, A2, B1, B2, C1 and C2 level. The VM level, which can be well tolerated without significant blood pressure and heart rate changes, is defined as threshold MV level for each individual patient.

3.3.2.2 Accommodation phase

The MV maneuvers will be performed in the morning session consisted 8 VM and in the afternoon session consisted 7 VM. Patients will be asked to perform VM from A1 level to C2 level gradually. Patients who do not reach the C2 level within 10 days will be excluded from the study.

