It is considered that sympathetic activity increased with reduction of venous return and decrease of cardiac preload in the syncopal period of VVS patients at first, and reflex activity of vagus nerve led to the decrease of heart rate and / or blood pressure at present. We think that the therapeutic effect of VM in VVS patients may be related to the regulation of autonomic nervous function [8]. HRV is a common index to evaluate autonomic function. We design the study to test if VM can be an eligible therapeutic option for VVS patients and observe the autonomic nervous function change by HRV indexes in VVS patients. To reduce the likelihood of inducing syncope by classical VM, a modified step-up graded VM (MVM) will be proposed to treat VVS patients by increasing expiration strength and breath-hold time gradually.

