**Objective**

1. To observe the safety and efficacy of a modified Valsalva maneuver (MVM) in VVS patients and find out a new way to treat VVS.

2. To discovery the pathogenesis of VVS and the potential mechanism of MVM on VVS.

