**Methods**

1. Study population

Inclusion criteria: we will recruit VVS patients aged between 18 to 80 years old with at least three lifetime syncopal spells associated with positive head-up tilt testing.

Exclusion criteria: Patients will be excluded if they have other causes of syncope, cannot give informed consent, have serious diseases or psychopath. Women who are pregnant, ready to pregnant, or breast-feeding a baby will be excluded.

2. Divided groups

VVS patients will be randomly divided into two groups: NVM group and MVM group, each 30 patients. Healthy control group (CON group) is 30 patients.

2.1 NVM group: Conventional therapy included: 1) Patient education for the importance of taking enough dietary salt and fluid in daily life. 2) Avoid medications such as diuretics and vasodilators.

2.2 MVM group: conventional treatment plus standard MVM for 50-60 minutes once a day for 30 days.

2.3 CON group: Age and gender matched healthy volunteers without syncope will be enrolled as healthy controls.

3. Study methods

All patients will give informed consent for participation in the study. Age, gender, body mass index, heart rate, blood pressure and biochemical indexes will be record at baseline in the three groups. Frequency and duration of syncope, syncope-induced trauma as well as disease history and current medications will be record in VVS patients.

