**Study flowchart and Study plan**

**Study flowchart**

Syncope patient: HUTT, Holter and randomized

Healthy volunteers: Holter

MVM group: Exclude patients who cannot reach C2 within 10 days at accommodation phase. Conventional treatment plus standard MVM for 30 days

NVM group: conventional treatment for 30 days

CON group

HUTT, Holter after 30 days treatment. Incidence of recurrent syncope during 12 months follow-up

Holter after 30 days

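### Randomised MVM patients who do not reach level C2 within 10 days leave the study, with no counterpart in NVM, so the between-group comparisons are no longer between the randomised groups

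*Protocol*

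**What the plan says.** The Study flowchart puts randomisation at the entry step: "Syncope patient: HUTT, Holter and randomized". Methods, Divided groups, gives the allocation: "VVS patients will be randomly divided into two groups: NVM group and MVM group, each 30 patients".

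Section 3.3.2.1 assigns the stepwise manoeuvre to MVM patients only. Section 3.3.2.2 then takes them from A1 up to C2 and adds: "Patients who do not reach the C2 level within 10 days will be excluded from the study". The flowchart repeats the rule under one group: "MVM group: Exclude patients who cannot reach C2 within 10 days at accommodation phase". The corresponding NVM line is only "NVM group: conventional treatment for 30 days".

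Sections 3.1 and 3.2 plan HUTT and Holter at baseline and after 30 days in all VVS patients. Section 3.4 counts the one-year recurrence follow-up from the end of the 30 days of therapy. Statistical analysis compares NVM and MVM by a chi-square test for HUTT positivity and a log-rank test for recurrence. The first objective is "To observe the safety and efficacy of a modified Valsalva maneuver (MVM) in VVS patients".

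**The concern.** Reaching C2 is not a baseline eligibility criterion. It is observed after allocation, in one group, and depends on how the patient responds to the assigned treatment. NVM patients who would also have failed the step-up stay in NVM because nothing tests them. Once such patients leave MVM, randomisation no longer makes the two analysed groups comparable, and a difference in HUTT positivity or recurrence can arise without any treatment effect.

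The wording removes patients from the study, not just from one analysis set. A statistical analysis plan could define an intention-to-treat population, but it could not recover a HUTT, a Holter recording or a year of syncope follow-up that was never collected. The problem therefore has to be solved in the protocol.

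Safety is a stated objective too. Patients who could not complete the step-up are the ones most informative about intolerance, and the protocol does not say how they are to be reported.

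**Working it through.** **The passages side by side**

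1. Order: randomisation (flowchart, first step), then threshold and accommodation (3.3.2.1, 3.3.2.2), then 30 days at C2 (3.3.2.3). The exclusion comes after randomisation.
2. Group: the flowchart states the rule for MVM only.
3. Conflict: 3.1 and 3.2 schedule HUTT and Holter after 30 days in all VVS patients, whereas 3.3.2.2 takes some of them out of the study. No sentence keeps the latter in follow-up.
4. Time origin: 3.4 counts follow-up from the end of therapy. Patients who do not reach C2 never start the 30-day phase at C2, so they have no defined start of follow-up. For those who do, accommodation can add up to 10 days before the 30 days, so MVM can be assessed up to 10 days later after randomisation than NVM.

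**Size of the effect, as an illustration**

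The protocol states no event rate, exclusion rate or power, so there is no figure to reproduce. Inputs:

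- 30 randomised per group (Methods, Divided groups) and P<0.05 (Statistical analysis), taken as two-sided.
- Assumed: no true effect; overall recurrence risk p = 0.50 in both groups; share of MVM excluded f = 0.20; recurrence risk q among the excluded varied from 0.30 to 0.80.
- Assumed: an uncorrected chi-square test on proportions, standing in for the log-rank test.

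Risk among MVM patients who stay: r = (p − f·q)/(1 − f). The spurious difference in favour of MVM is p − r.

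- q = 0.80: r = (0.50 − 0.16)/0.80 = 0.425, difference 7.5 points
- q = 0.60: r = (0.50 − 0.12)/0.80 = 0.475, difference 2.5 points
- q = 0.50: r = (0.50 − 0.10)/0.80 = 0.500, difference 0
- q = 0.30: r = (0.50 − 0.06)/0.80 = 0.550, difference −5.0 points (against MVM)

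Exact binomial enumeration of the test, with the number excluded also binomial, gives the chance of a significant result in favour of MVM:

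| Recurrence among the excluded | Spurious difference | Falsely significant MVM benefit |
|---|---|---|
| 80% | 7.5 points | 8.1% |
| 60% | 2.5 points | 3.9% |
| 50% | 0 | 2.6% |
| 30% | −5.0 points | about 1.0% |
| All 30 v 30 analysed as randomised | 0 | 2.6% |

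Other exclusion rates: 10% excluded with 70% recurrence gives 2.2 points and 3.8%; 30% excluded with 80% recurrence gives 12.9 points and 14.9%. Replacing excluded patients to bring MVM back to 30 does not help: with 20% excluded and 80% recurrence the figure is 8.6%.

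**The case against.** The strongest reply concerns direction. A reader might infer that the efficacy comparisons are certainly biased towards MVM because the removed patients are those who react most to straining. The documents do not say this. Section 3.3.2.2 gives no reason for failing to reach C2. The haemodynamic criterion in 3.3.2.1, "The VM level, which can be well tolerated without significant blood pressure and heart rate changes, is defined as threshold MV level", defines the individual threshold level, not failure of accommodation. In patients aged 18 to 80, weak expiration, short breath-hold or poor adherence could also be the cause. If non-reachers had average risk there would be no bias in the estimate, and with lower risk it would reverse. This stands. What remains is plausibility: 3.3.2.1 ties the level to tolerance, and the Background says of the design, "To reduce the likelihood of inducing syncope by classical VM, a modified step-up graded VM (MVM) will be proposed".

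A reader might also infer that safety is assessed only in patients already shown to tolerate the manoeuvre, or that a safety comparison between groups is biased. Neither is supported. No between-group safety test is planned, NVM does not perform the manoeuvre, and nothing says that events before exclusion are discarded. Only a risk of under-reporting stands.

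Finally, it can be argued that 3.1 and 3.2 already keep every VVS patient in the HUTT and Holter assessments. Exclusion from the study most naturally overrides those sentences, but the tension is real and is itself a reason to amend the text.

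**Conclusion.** The point holds. The exclusion is made after randomisation, in one group and on response to the assigned treatment, so the planned HUTT and recurrence tests do not compare the randomised groups. That conclusion does not depend on the direction of the bias. Bias in favour of MVM is likely if non-reachers are more prone to syncope, but this is an inference.

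The size is unknown. On the assumptions shown, with 20% excluded, the chance of a false MVM benefit runs from about 1.0% to 8.1% against a nominal 2.6%. The figures rest on assumed risks and on a chi-square stand-in, and they show scale only. For safety, the supportable conclusion is that intolerance may be under-reported in the MVM profile. This should be corrected before the trial starts, because outcomes not collected cannot be restored at analysis.

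**What to change.** In section 3.3.2.2 and in the flowchart, replace exclusion from the study with wording to this effect: *patients who do not reach C2 remain in the MVM group as randomised, have the follow-up HUTT and Holter and the 12-month syncope follow-up, and are analysed in the MVM group.*

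To make this workable:

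- Count the timing of the follow-up HUTT and Holter, and the time to recurrence, from randomisation in both groups. Align 3.1, 3.2, 3.4 and Statistical analysis accordingly.
- Report how many patients did not reach C2, the reasons, and the events during the threshold and accommodation phases.
- Show the patients who reached C2 only as a secondary analysis, labelled non-randomised.

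How non-reachers are treated after day 10 is for the investigators to decide.

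The cost is the text changes in these sections, follow-up of a few more patients who are already enrolled, and possibly a smaller observed effect.

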3.3.2.3 Standardized MVM therapy phase

The MVM patients will be asked to perform 15 MV at C2 level daily about 50-60 minutes for 30 days.

3.4 Follow-up

Recurrence syncope of VVS patients will be observed during the follow-up of one year after 30 days therapy.

**Statistical analysis**

Continuous variables will be presented as mean ± standard deviation (SD). Continuous data with normal distribution will be assessed by Student’s *t*-test or one-way ANOVA with Post Hoc test (Bonferroni) as indicated, and non-normal distribution data will be tested by two-tailed Mann–Whitney U test or Kruskal-Wallis non-parametric test as indicated for the baseline characteristics of the three groups. The Chi-square test will be used to compare the ratio or percentages of categorical variables of the three groups. The Chi-square test will be used to compare the positive rate of HUTT at baseline and after 30 days treatment between NVM and MVM groups. The incidences of recurrent syncopeduring 12 months follow-up of NVM and MVM groups will be compared by log rank test of Kaplan-Meier curve. HRV indexes among the three groups will be assessed by one-way ANOVA with Post Hoc test (Bonferroni) for normal distribution data, Kruskal-Wallis non-parametric test for non-normal distribution data. HRV indexes between baseline and after 30 days treatment will be assessed by Student’s *t*-test for normal distribution data, two-tailed Mann–Whitney U test for non-normal distribution data. The relationship between HUTT and recurrent syncope, HRV and recurrent syncope during 12 months follow-up in VVS patients will be assessed by univariable and multivariable Cox proportional hazards models after 30 days intervention. Receiver operating characteristic (ROC) curves of HRV values at 30 days after intervention will be used to predict 12 months follow-up recurrent syncope. The cutoff values of HRV will be derived from ROC curve analysis by maximizing the sum of the sensitivity and specificity. All statistical analyses will be performed with SPSS version 19.0. *P*<0.05 is considered statistically significant.

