**Expected results**

1 VVS患者存在自主神经功能失调紊乱。

The data will be similar at baseline among the three groups. Positive rate of HUTT will be lower in the MVM group than in the NVM group after 30 days treatment. The incidence of rate of recurrent syncope will be lower in the MVM group than in the NVM group during 12 months follow-up. VVS patients have autonomic nervous function imbalance by HRV analysis among the three groups and between baseline and after 30 days treatment. The underlying mechanism of MVM treating VVS is to improve autonomic nervous function.

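### Recurrent syncope is compared by an unadjusted log-rank test although prior syncope frequency is recorded; adjusting for it would cost almost nothing and recover some efficiency

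*Protocol*

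**What the plan says.** The Protocol's Statistical analysis section fixes the between-arm analysis of recurrence: "NVM and MVM groups will be compared by log rank test of Kaplan-Meier curve". It names no covariate, stratum or hazard ratio for treatment.

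The same section does plan univariable and multivariable Cox models, but for a different question: "The relationship between HUTT and recurrent syncope, HRV and recurrent syncope during 12 months follow-up in VVS patients". Arm and prior syncope frequency are not named in them.

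Under Methods, 3. Study methods, directly after the list of baseline measurements, the protocol states: "Frequency and duration of syncope, syncope-induced trauma as well as disease history and current medications will be record in VVS patients". Under Methods, 2. Divided groups: "VVS patients will be randomly divided into two groups: NVM group and MVM group, each 30 patients". No stratification factor is given. The entry criterion is "at least three lifetime syncopal spells associated with positive head-up tilt testing", with no upper limit. Follow-up for recurrence is one year after the 30-day therapy (section 3.4).

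The expectation is directional only: "The incidence of rate of recurrent syncope will be lower in the MVM group than in the NVM group during 12 months follow-up". No recurrence rate, hazard ratio, event count or power is stated.

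**The concern.** The outcome is further occurrence of the event whose past frequency is already recorded. The entry rule sets a floor of three lifetime spells and no ceiling, so prior burden may differ widely between patients. It is therefore a natural candidate predictor, it precedes randomisation, and neither the randomisation nor the treatment comparison uses it.

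If prior frequency is prognostic, two things follow in a trial of 60. An unadjusted test has less average power than one that accounts for it. And the one result obtained depends more on how high-frequency patients happen to fall between the arms. The HUTT and HRV values at 30 days cannot take its place, because they are measured after randomisation and may themselves be affected by treatment.

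**Working it through.** The plan has no power or sample-size figure to reproduce. The check therefore asks what adjustment would change under stated assumptions.

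**Inputs from the protocol:** 30 per arm, 12 months of follow-up, significance level 0.05 (taken as two-sided; the protocol does not say for this test).

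**Assumptions:** control 12-month recurrence 30% to 50% (to 60% in the formula check); treatment hazard ratio (HR) 0.3 to 0.5 (to 0.6 in the formula check); prognostic HR 1.0 to 2.5 per SD of prior frequency; exponential times; all 60 patients followed for the full year.

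**1. Background power of the log-rank test.** Events = 30 × (pc + pt), with pt = 1 − (1 − pc)^HR. Power = Φ(√events / 2 × |ln HR| − 1.96).
- pc = 0.5, HR = 0.4: pt = 1 − 0.5^0.4 = 0.242; events = 30 × 0.742 = 22.3; power = Φ(2.16 − 1.96) = 58%.
- pc = 0.3, HR = 0.5: pt = 1 − 0.7^0.5 = 0.163; events = 30 × 0.463 = 13.9; power = Φ(1.29 − 1.96) = 25%.
- Over the whole assumed range: 12 to 31 events, power 16% to 86%.

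**2. Chance imbalance.** The standardised mean difference between arms has SD √(2/30) = 0.258. The probability that it exceeds 0.25 in either direction is 2 × [1 − Φ(0.25/0.258)] = 33%; that it exceeds 0.5, 5.3%.

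**3. Average power, unadjusted against adjusted.** Simulation of 10,000 trials per scenario. Each patient's hazard is λ × exp(g·z + ln(HR)·arm), with z standard normal, g the log prognostic HR, and λ set so that control recurrence equals pc. The log-rank (score) test is compared with the likelihood-ratio test for arm in a Cox model containing z. The Monte Carlo standard error of one power figure is at most √(0.25/10,000) = 0.5 points.

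| Prognostic HR per SD | pc 50%, HR 0.4: log-rank → adjusted | Difference | pc 30%, HR 0.5: log-rank → adjusted | Difference |
|---|---|---|---|---|
| 1.0 | 56.0% → 56.0% | 0.0 | 23.5% → 24.8% | 1.3 |
| 1.3 | 54.8% → 56.0% | 1.2 | 23.1% → 24.7% | 1.6 |
| 1.5 | 53.8% → 56.7% | 2.9 | 23.0% → 25.0% | 2.0 |
| 2.0 | 49.2% → 57.1% | 7.9 | 22.2% → 25.4% | 3.2 |
| 2.5 | 43.8% → 57.9% | 14.1 | 20.8% → 26.1% | 5.3 |

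The 1.3 points in the right-hand column at prognostic HR 1.0 cannot be a gain from prognosis; they reflect the adjusted test being slightly liberal with few events.

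**4. Type I error.** Unadjusted: 4.8% to 5.3% throughout. Adjusted: 4.9% to 5.4% at 50% recurrence (about 30 events under the null) and 5.4% to 5.9% at 30% recurrence (about 18 events).

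**5. Power given an imbalance above 0.25 SD** (pc 50%, HR 0.4).
- Prognostic HR 1.5: log-rank power is 39% when the imbalance goes against MVM and 67% when it favours MVM; the adjusted test gives about 55% in both cases.
- Prognostic HR 2.0: 26% and 72%; adjusted 53% and 56%.

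**The case against.** The strongest reply is that nothing here is wrong. A log-rank test is a valid comparison of randomised arms, and covariates and a hazard ratio are often left to a SAP, which is not shown. The first half stands: preferring an adjusted model is a matter of efficiency. The second half stands only in part. The protocol is not silent; it names the test for this comparison and reserves Cox models for other questions. A SAP could still add the adjustment.

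Four stronger readings are tempting and are not supported:
- *The comparison is biased or its error rate inflated.* Overall type I error is near 5%. Chance imbalance is already part of the test's sampling distribution, so the contrast in step 5 explains how one result can swing; it is not a harm on top of the power loss in step 3.
- *The unadjusted effect is a wrong estimate.* Part of the gap is that marginal and covariate-conditional hazard ratios are different quantities.
- *No effect size will be available.* The Kaplan-Meier curves give each arm's 12-month recurrence. What is not planned is a treatment hazard ratio with an interval.
- *The main outcome is mishandled.* The protocol names no primary outcome; HUTT at 30 days and 12-month recurrence stand side by side in the Abstract.

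It is also fair to say that the prognostic strength of prior frequency is assumed, with no support in the document. The largest gains need a hazard ratio of 2.0 or more per SD.

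**Conclusion.** The point holds as a modest, low-cost improvement. The protocol fixes an unadjusted test for recurrence while recording a plausible prognostic variable that neither the randomisation nor the treatment analysis uses.

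At 50% control recurrence and a treatment hazard ratio of 0.4, the average power given up is nil if prior frequency is not prognostic, 1 to 3 points at 1.3 to 1.5 per SD and about 8 points at 2.0. At 30% recurrence and a hazard ratio of 0.5 it is about 2 to 3 points at 1.3 to 2.0, partly an artefact of the liberal adjusted test. The second cost is that a single result leans on the draw of patients when arms differ by more than 0.25 SD, which happens in about one trial in three.

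All sizes rest on the assumed recurrence rate, treatment effect and prognostic strength. The conclusion that the unadjusted test remains valid depends only on randomisation with all randomised patients analysed.

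**What to change.** In the Statistical analysis section, prespecify a Cox model for 12-month recurrence with arm and one baseline covariate, prior syncope frequency, reporting the treatment hazard ratio with 95% CI. Keep the Kaplan-Meier curves and the log-rank test as supportive.

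The covariate needs a definition, since the protocol does not say whether frequency means a lifetime count, a rate or a recent count. One workable form is the log of a count recorded before randomisation, over the same reference period for every patient. A log-rank test stratified by prior frequency is an alternative, though it gives no hazard ratio by itself.

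The cost is a sentence or two, with no new measurement as long as frequency is recorded in a uniform way. The downside is a slightly liberal test when events are few (5.4% to 5.9% at about 18 events), so the model should carry this one covariate and no more. With about 12 to 31 events expected under the assumed ranges, adjustment does not make up for the small number of events.

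### The three-group HRV comparison omits age and gender, the factors on which controls are matched; adjusting for both would be a cheap, minor gain in efficiency if they influence HRV

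*Protocol*

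**What the plan says.** Protocol, Methods, section 2 (Divided groups) sets the group sizes: "VVS patients will be randomly divided into two groups: NVM group and MVM group, each 30 patients", and "Healthy control group (CON group) is 30 patients". Section 2.3 describes how controls are chosen: "Age and gender matched healthy volunteers without syncope will be enrolled as healthy controls". It describes no pairs, matched sets, matching ratio or age tolerance. The patients' age range is wide (section 1: "we will recruit VVS patients aged between 18 to 80 years old"). Section 3 (Study methods) has age and gender recorded at baseline in all three groups.

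Statistical analysis then fixes the test: "HRV indexes among the three groups will be assessed by one-way ANOVA with Post Hoc test (Bonferroni) for normal distribution data", and "Kruskal-Wallis non-parametric test for non-normal distribution data". Neither test contains age, gender or a matching term. Multivariable modelling is named only for the Cox models of recurrent syncope. The significance threshold is P < 0.05. The Protocol gives no effect size, SD or power for HRV.

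**The concern.** Matching on age and gender is done because those factors are thought to affect the outcome. One-way ANOVA leaves whatever variance they explain in the residual, which has two consequences.

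- The test is less sensitive than one that includes the two factors.
- When matching is close, age and gender add little to the real sampling variation of the patient-control difference, but the ANOVA standard error still includes their variance. The test is then conservative.

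At stake is the pathogenesis part of objective 2. Among the planned analyses, the three-group HRV comparison is the one that sets patients against healthy people, and it rests on 30 controls. A real autonomic difference could be missed although the data to detect it more reliably are already collected.

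**Working it through.** The Protocol has no HRV power figure to reproduce. The group sizes agree with the abstract: 30 + 30 = 60 patients, plus 30 controls.

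**Inputs from the Protocol.** Three groups of 30; alpha 0.05, or 0.05/3 = 0.0167 per pair under Bonferroni; ages 18 to 80.

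**Assumptions.** R2, the share of HRV variance explained by age and gender, is ranged from 0 to 0.5. The true patient-control difference is 0.5 or 0.6 SD. Tests are two-sided.

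**Closed form, one arm against controls (30 v 30).** Adjustment reduces the residual SD by the factor sqrt(1 - R2), so the unadjusted standard error is larger by 1/sqrt(1 - R2). The difference detectable with 80% power at alpha 0.05 is (1.96 + 0.84) × sqrt(2/30) × sqrt(1 - R2) = 0.72 × sqrt(1 - R2) SD.

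| R2 | SE ratio, unadjusted/adjusted | Detectable difference, adjusted (SD) | Power at 0.5 SD, unadjusted v adjusted |
|---|---|---|---|
| 0 | 1.00 | 0.72 | 49% v 49% |
| 0.1 | 1.05 | 0.69 | 49% v 53% |
| 0.2 | 1.12 | 0.65 | 49% v 58% |
| 0.3 | 1.20 | 0.61 | 49% v 64% |
| 0.5 | 1.41 | 0.51 | 49% v 78% |

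**Simulation of the three-group F test at 0.6 SD.** Ages were uniform on 18-80 and gender 50/50; 60 patients were randomised 30/30. In the matched case, each of 30 controls took the age and gender of one patient from each adjacent pair after sorting by gender and age. In the unmatched case, controls were drawn at random. Ranges cover separate runs.

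| R2 | Matched controls: planned v adjusted | Unmatched controls: planned v adjusted |
|---|---|---|
| 0.1 | 65-66% v 69-70% | 65-66% v 69% |
| 0.2 | 66-67% v 75-76% | 65% v 75% |
| 0.3 | 67-68% v 80-82% | 66% v 80-81% |
| 0.5 | 69% v 92-93% | 64-66% v 92% |

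The gain is nearly the same in both columns. At R2 = 0.3, for example, it is about 82 - 68 = 14 points with matching and 81 - 66 = 15 without. It is therefore the ordinary benefit of adjusting for prognostic covariates. At R2 = 0 there is none: a separate simulation at 0.5 SD gave 50% for both tests.

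**What matching adds: the error rate when there is no true difference.** With close matching, the planned F test rejects about 4% of the time at R2 = 0.1, 3% at 0.3 and 2% at 0.5, against a nominal 5%. The adjusted test stays at about 4.4-5.2%. With unmatched controls the planned test is near nominal, at 4.5-5.2%. The Bonferroni MVM-CON contrast behaves in the same way under close matching: against a nominal 1.67% it rejects 1.1%, 1.1%, 0.7% and 0.3% at R2 = 0.1, 0.2, 0.3 and 0.5 as planned, and about 1.4-1.7% when adjusted.

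Kruskal-Wallis was not simulated. It also omits both factors, so the same reasoning applies in direction, but these figures are for ANOVA.

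**The case against.** The strongest objection is that the power figures do not measure a failure to respect matching, since unmatched controls give almost the same gain. This stands. A reader might infer that power is lost because matched data are analysed as unmatched. The comparison above does not support that: matching slightly raises the planned test's power, and only the conservative error rate is specific to it.

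The size of that conservatism also depends on how close the matching is. The simulation copied ages and genders from patients, whereas the Protocol describes no procedure, and 30 controls beside 60 patients reads as group matching. A reader might therefore go further and ask for a paired or matched-set test. No pairs or sets are defined, so the text does not call for one.

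The loss depends on R2, which the Protocol does not give: it is nil at R2 = 0 and about 4-5 points at 0.1. The NVM and MVM arms are randomised, not matched to each other, so the matching aspect concerns the contrasts with controls. Objective 2 also covers the mechanism of MVM, which other planned HRV analyses address.

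Finally, covariate adjustment is often left to a statistical analysis plan, which is not shown. That answers a complaint of missing detail. It does not fully answer this point, because the Protocol itself names a specific unadjusted test.

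**Conclusion.** The point holds as a minor efficiency improvement. The planned HRV test omits two recorded factors that the design itself treats as relevant, and an adjusted model would be more powerful if those factors matter. At 0.6 SD the F-test gain is about 4-5 percentage points at R2 = 0.1, 12-14 at 0.3 and 24 at 0.5. Both the effect size and R2 are assumptions.

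The documents do not support saying outright that the standard errors are too large or that power is lost. That requires a material R2 and, for the error-rate part, reasonably close matching; neither is stated. Nor is the planned comparison invalid: it adds no bias and no excess of false positives, and a significant result from it would not be undermined by this point. HUTT positivity and recurrent syncope, which carry the efficacy question, are unaffected.

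**What to change.** In Statistical analysis, replace the three-group one-way ANOVA for HRV with a linear model, HRV index = group + age + gender, and take the Bonferroni pairwise contrasts from the adjusted means. For skewed indexes, fit the same model to log-transformed values in place of Kruskal-Wallis, or to ranks where the log cannot be taken (for example, pNN50 of zero).

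The cost is one sentence of wording and no new data, and the model is standard in SPSS 19. Residual degrees of freedom go from 90 - 3 = 87 to 85. The model assumes a linear age effect, which can be checked with a plot of HRV against age.
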